#### EA group

Subjects in this group will receive EA treatment. The following acupoints were selected: local acupoints: *Baihui* (GV20) and *Shenting* (GV24); distal acupoints: bilateral *Shenmen* (HT7) and bilateral *Sanyinjiao* (SP6). After skin disinfection, sterile adhesive pads will first be fixed on the acupoints, and the acupuncture needles will be inserted through the adhesive pads into the skin. Needle insertion will follow an angle of 30° along the anterior-posterior midline for GV20 and GV24. Perpendicular punctures will be used for HT7 and SP6. Acupuncturists will manipulate the needle until patients experience the *de qi* sensation (manifesting as soreness, fullness, heaviness, and numbness when lifting, thrusting, or rotating the needle). There are three sets of electrodes connected. One set of two electrodes of the EA device are connected at GV20 and GV24. Another two sets of electrodes are connected at the ipsilateral HT7 and SP6. The electroacupuncture intervention will apply 10-Hz continuous waves, and the current will range from 1 to 5 mA. The intensity will be adjusted based on the tolerance of each patient. Each session will last 30 min and be performed every other day for 4 successive weeks, for a total of 14 sessions.

#### SZRD group

Subjects in this group will receive SZRD treatment. SZRD consists of 5 herbs, including Suanzaoren, Fuling, Zhimu, Chuanxiong, and Gancao, in the following concentrations: 41%, 20%, 20%, 13%, and 6%, respectively. Patients will be administered SZRD granules in one bag (3.4 g per bag) dissolved in boiling water two times daily for 4 successive weeks.

#### EA & SZRD group

Subjects in this group will receive the EA and SZRD treatments. The procedures for the EA and SZRD treatments will be the same as those for the EA group and SZRD group. EA will last 30 min in each session, which will be performed every other day for 4 successive weeks, for a total of 14 sessions. SZRD treatment will be given two times daily for 4 successive weeks.

#### Sham group

Subjects in this group will receive sham EA treatment with sham acupuncture needles. The acupoints selected, manipulation procedures, electrode placements, and other treatment settings will be the same as in the EA group, while the effects of *de qi* will not be produced through skin penetration or needle manipulation. Furthermore, all parameters of the electrical stimulation will be set to 0. After retaining the needles for 30 min, acupuncturists will remove all needles using dry cotton balls and press the acupoints to provide patients with the sensation of a ‘real’ needle being withdrawn from the skin. Each session will last 30 min and will be performed every other day for 4 successive weeks.

### Criteria for discontinuing or modifying allocated interventions {11b}

If participants feel that their diseases are not improving, they will be free to withdraw from the clinical study and choose other therapies. Participants who meet the following criteria could be discontinued from receiving the interventions:
They develop a serious disease such as heart disease, pneumonia, or stroke during the trial;They receive other treatments for insomnia such as other medicine, moxibustion, or massage, during the study;They experience serious side effects;They refuse to continue to participate in the RCT;They are lost to follow-up; orThey do not comply with the study protocol.

### Strategies to improve adherence to interventions {11c}

Frequent follow-up telephone calls and messages on the WeChat platform will be important aspects for improving adherence to interventions.

### Relevant concomitant care permitted or prohibited during the trial {11d}

Given the history of stroke, all participants will continue to take basic Western medications for the secondary prevention of stroke during the study. The name, dose, and usage of the medications will be recorded.

### Provisions for post-trial care {30}

If the condition of a subject worsens after the trial or is accompanied by severe complications or serious adverse reactions, the specialist will take medical measures to deal with the harm based on the subject’s condition. The treatments will be free.

### Outcomes {12}

#### Primary outcomes

The following primary outcomes will help us to assess whether the combination of EA with SZRD is more effective in insomnia in post-stroke patients.

##### Pittsburgh Sleep Quality Index

The PSQI is a self-rating questionnaire scale with 19 self-rated items and five other-rated items measuring sleep quality and disturbances over a period of 1 month [27]. The self-rated items include the following seven subscales: sleep quality, sleep latency, sleep duration, habitual sleep efficacy, sleep disturbances, use of sleeping medication, and daytime dysfunction. Each subscale will be answered by patients on a 0 to 3 response category scale, and the total score of the PSQI can range from 0 to 21 points. A lower score indicates a better quality of sleep. The assessment will be performed at baseline (before treatment) and during the 4th week of the intervention, as well as at the 8th and 12th weeks of follow-up.

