#### Exclusion criteria

Participants who meet the following criteria will be excluded from the trial:
Had insomnia before stroke;Insomnia by poor sleep conditions [26];Have diagnoses of other sleep disorders, such as narcolepsy, obstructive sleep apnoea syndrome, or restless legs syndrome;Have neurological or psychiatric diseases;Have severe diabetes; hypertension; severe liver, kidney, or thyroid dysfunction; and severe cardiac insufficiency;Are unable to read, understand, and complete the forms or use the rating scales;Have implants that could interfere with EA or a history of hypersensitivity to EA;Had received TCM in the previous 1 month;Had participated in other trials;Are taking sleep-affecting diet or medication; orAre pregnant or preparing for pregnancy.

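### The PSQI total contains a sleeping-medication component, and only the two SZRD arms knowingly take an insomnia formula, so assigned treatment can add 0 to 3 points to the week-4 score

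*Protocol article*

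**What the plan says.** All references are to the protocol article.

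- **The score.** The Pittsburgh Sleep Quality Index section lists seven self-rated components, ending with "habitual sleep efficacy, sleep disturbances, use of sleeping medication, and daytime dysfunction". On scoring it says: "Each subscale will be answered by patients on a 0 to 3 response category scale". The total runs from 0 to 21, and "A lower score indicates a better quality of sleep". The recall is described as "measuring sleep quality and disturbances over a period of 1 month".
- **The visits.** The PSQI is taken at baseline, during week 4, and at weeks 8 and 12.
- **The treatment.** The SZRD group section states: "Patients will be administered SZRD granules in one bag (3.4 g per bag) dissolved in boiling water two times daily for 4 successive weeks". The EA & SZRD group receives the same granules. The Background presents SZRD as a formula for insomnia.
- **The other arms.** Table 1 gives the EA and sham groups no herbs and shows no placebo granules.
- **Blinding.** Section 17a says that participants in the two SZRD arms cannot be blinded.
- **Other sleep medicines.** One exclusion criterion reads "Are taking sleep-affecting diet or medication", and section 11b makes other insomnia medicine during the study a ground for discontinuation.

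The article does not say whether study granules count in the sleeping-medication component. It describes no version of the total without that component.

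**The concern.** The entry and discontinuation rules should hold the sleeping-medication component near zero at baseline in every arm, and in the EA and sham arms throughout. At week 4 its main systematic source of variation would then be whether the patient was allocated SZRD. A patient who regards the granules as medicine taken for sleep reports worse sleep quality simply by taking the assigned treatment. Another patient in the same arm may leave them out.

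This matters in three ways:

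- **Main question.** The Objectives ask whether the combination beats each therapy alone. EA & SZRD versus EA is half of that question and is exposed. SZRD versus EA is exposed too.
- **Order of testing.** Section 20a compares each treatment with sham first, and compares the treatment groups with each other only if a difference is found. A shift against the SZRD arms versus sham could therefore stop the trial from reaching the comparison it was designed for.
- **Course over time.** Because the granules stop at week 4, an inflated week-4 score that later falls could look like delayed benefit.

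**Working it through.** **Inputs from the article**

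- Sample size section: 9.21 (SD 4.05) versus 13.18 (SD 4.32) at 4 weeks; α = 0.05 two-sided; power 0.9; 25 per group before drop-out; 20% drop-out; 60 per group recruited.
- Section 20a: important difference 1.14–1.75; response is a fall of 2 or more points.
- PSQI section: each component scores 0–3, total 0–21.

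**Step 1: reproduce the plan's own figure.** δ = 13.18 − 9.21 = 3.97. Pooled SD = √((4.05² + 4.32²)/2) = 4.187. With n = (1.960 + 1.282)² × 2σ²/δ²:

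- σ = 4.187 gives 23.4, so 24 per group.
- σ = 4.32 gives 24.9, so 25 per group.

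The stated 25 reproduces. This point does not rest on an error in the sample size.

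**Step 2: bound the shift.** One component can add at most 3 points. If a share p of patients in an SZRD arm count the granules, and each who does scores s on the component (s up to 3), the arm mean rises by p × s, which lies between 0 and 3. The article fixes neither p nor s. Relative to the plan's own yardsticks, the ceiling is:

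- 3/3.97 = 76% of the planning difference;
- 3/2 = 1.5 times the response threshold;
- 3/1.75 = 1.7 to 3/1.14 = 2.6 times the important difference.

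At the ceiling, a patient who improves by 4 points on the other six components nets 4 − 3 = 1 and is classed as a non-responder.

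**Step 3: which contrasts and visits are affected**

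| Contrast at week 4 | Effect of the shift |
|---|---|
| SZRD vs sham; EA & SZRD vs sham | Benefit understated |
| EA & SZRD vs EA; SZRD vs EA | SZRD-containing arm looks worse |
| EA & SZRD vs SZRD | Largely cancels |
| EA vs sham | None |

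Week 4 is the time point used for planning. The visit falls during that week, so a 1-month recall covers most of the dosing period and possibly a few days before it. By weeks 8 and 12 dosing has ended and the shift should largely be gone.

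**Step 4: illustrate the size against sham.** Take 48 per arm (60 × 0.8), so SE = 4.187 × √(2/48) = 0.855. Observed difference = 3.97 − shift. Power is for an unadjusted two-sided 5% two-sample test.

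| Shift | Observed difference | Power, 48 per arm | Power, 60 per arm | n per group for 90% |
|---|---|---|---|---|
| 0 | 3.97 | 0.996 | 0.999 | 24 |
| 1 | 2.97 | 0.935 | 0.973 | 42 |
| 2 | 1.97 | 0.635 | 0.731 | 95 |
| 3 | 0.97 | 0.205 | 0.245 | 392 |

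**Step 5: illustrate EA & SZRD versus EA with no true difference.** With 48 per arm, a shift of 1, 2 or 3 points would make the combination look significantly worse with probability of about 0.22, 0.65 or 0.94 on the same unadjusted test.

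The planned analysis is repeated measures with Bonferroni correction, so steps 4 and 5 show scale and direction, not the trial's actual power.

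**The case against.** The strongest reply is that the article states nothing false. It lists the PSQI components and range correctly on its own terms, and completion instructions usually sit in the case report form or an assessor manual. Only the component's label is given, so neither whether herbal granules fall under it nor how daily use is scored can be read from the text. That stands as a limit on size: the shift may be zero. It does not remove the point, because the total as defined includes the component, and it is taken by two unblinded arms on an insomnia formula alongside two arms kept off such medicines.

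Other objections also hold in part:

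- Polysomnography is also listed as primary, is measured at 4 weeks and has no such component. The Insomnia Severity Index is taken at weeks 2, 4, 8 and 12, and no medication part is described for it. Discordance with these could reveal the artefact. The sample size, however, rests on the PSQI.
- For the combination the bias is conservative. It cannot produce a false claim that EA & SZRD is superior; the risk is a missed or understated effect, or a comparison tilted towards EA.

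A reader might infer that SZRD will add 3 points, or that a real advantage of the combination over EA will be reversed. The documents support neither. Three points needs every patient to count the granules and to score the maximum, and the article gives no expected difference between EA & SZRD and EA from which a reversal or a specific loss of power could be calculated.

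**Conclusion.** The point holds as a possible bias tied to the assigned arm in the week-4 PSQI total, of 0 to 3 points and unknown size. It works against SZRD and EA & SZRD versus sham and versus EA. It largely cancels between EA & SZRD and SZRD, should largely fade once dosing ends, and leaves polysomnography untouched.

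Even a 2-point shift would exceed the plan's own important difference and would cut the illustrative power against sham from 0.996 to about 0.64. That rests on the planning SDs, 20% drop-out, an unadjusted test, and an assumed shift that the article neither supports nor excludes. It does not follow that the trial's conclusions are invalid. What follows is that a week-4 total collected without a rule on the granules cannot separate treatment effect from the way patients answer one component.

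**What to change.** 1. State on the PSQI form and in assessor training that study granules are not counted in the sleeping-medication component, which then records non-study medicines only.
2. Pre-specify the six-component total without that component (6 × 3 = 18, so 0–18) as a sensitivity analysis, for all patients and all contrasts.
3. If patients have already been assessed without the instruction (recruitment began in April 2020 according to Trial status), apply the 0–18 total uniformly to everyone. Using 0–18 for earlier patients and 0–21 for later ones would put two endpoint definitions into one comparison.

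**Cost.** A routine protocol amendment, since section 25 sends changes to outcomes or analyses to the ethics committee, plus a line on the form, a training note and one extra analysis. Component scores must be entered, not only the total. The 0–18 score differs slightly from the published PSQI, so the 1.14–1.75 important difference and the 2-point response threshold do not carry over to it exactly. No treatment rule changes.

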##### Polysomnography

PSG (Curative Medical Inc, Santa Clara, CA, USA) is used to objectively estimate sleep [28]. It records quantifiable data during sleep, such as total sleep time, sleep onset latency, waking after sleep onset, rapid eye movement, and non-rapid eye movement sleep. In this study, all patients will be assessed for two nights (one night at baseline and one night at 4 weeks post-treatment) in a specialized sleep laboratory. During the assessment process, the sleep time of participants will be based on their habit. Standard equipment will record sleep conditions from 22:00 to 7:00 for each assessment. All PSG data will be further analysed by Acumen 7 EV 2.11 software.

#### Secondary outcomes

The following secondary outcomes will help us to determine whether participants with post-stroke insomnia in the EA & SZRD group show greater improvements in sleep quality and other related symptoms than the other three groups after the therapies.

##### Insomnia Severity Index

The ISI is a self-report questionnaire designed to assess the degree of insomnia and the associated functional impairments [29]. The total score on the ISI can range from 0 to 28 points. A score of 0 to 7 indicates no clinically significant insomnia. A score of 8 to 14 is regarded as sub-threshold insomnia. A score of 15 to 21 is regarded as clinical insomnia of moderate severity. More than 22 points is regarded as severe clinical insomnia. The assessment will be performed at baseline (before treatment) and during the 2nd and 4th weeks of the intervention, as well as at the 8th and 12th weeks of follow-up.

##### Hospital Anxiety and Depression Scale

The HADS is a brief assessment used to measure current anxiety and depressive symptoms in a non-psychiatric hospital patient [30]. The HADS comprises two independent seven-item subscales for anxiety and depression. More than 11 points on either subscale indicate the probable presence of the mood disorder. The assessment will be performed at baseline (before treatment) and during the 2nd and 4th weeks of the intervention, as well as at the 8th and 12th weeks of follow-up.

##### National Institutes of Health Stroke Scale

The NIHSS is a stroke-specific quantitative scale used to assess neurological deficits [31]. Each participant will be assessed by a trained, certified investigator at baseline (before treatment) and during the 2nd and 4th weeks of the intervention, as well as at the 8th and 12th weeks of follow-up. A higher score indicates a more severe neurological deficit.

##### Brain magnetic resonance imaging (MRI)

MRI is a non-invasive imaging method to detect features of brain tissue [32]. In particular, MRI is a well-suited technique to visualize and analyse the anatomical properties and abnormalities in the brain. Each participant will be assessed at baseline (before treatment) and during the 4th week of the intervention.

##### Functional magnetic resonance imaging (fMRI)

fMRI is another non-invasive technique that is used to track metabolic activity in the brain. Abnormal fMRI might serve as a potential neuromarker for insomnia [33]. Each participant will be assessed at baseline (before treatment) and during the 4th week of the intervention.

##### Nocturnal concentration of melatonin (MLT)

Melatonin coordinates circadian rhythms and regulates sleep function [34]. Blood samples of patients will be collected at 3:00 a.m. in a dimly lit environment to diminish the impact of light on the secretion of melatonin. Each participant will be assessed at baseline (before treatment) and during the 4th week of the intervention.

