Therefore, we propose to conduct a clinical RCT on EA plus SZRD for the treatment of post-stroke insomnia. We designed a randomized, four-group, and single-blinded clinical trial with a 4-week treatment period and a 12-week follow-up period. Based on TCM theory and previous studies, *Shenmen* (HT7), *Sanyinjiao* (SP6), *Baihui* (GV20), and *Shenting* (GV24) are the most frequently selected acupoints for the treatment of post-stroke insomnia, and local acupoint stimulation can improve the curative effect when combined with distal acupoints [57, 58]. We also emphasize the experience of the “*de qi*” sensation during the intervention. There have been differences in efficacy between low-frequency and high-frequency electrical stimulation in EA therapy [59, 60]. Accumulating data have shown that low-frequency EA is effective for complications related to stroke, such as insomnia, epilepsy, and pseudobulbar palsy [61–63]. We selected a 10-Hz frequency of EA to treat insomnia after stroke in this trial. Preliminary analyses have indicated that different types of sham acupuncture may have different effect sizes, and a meta-analysis showed that sham devices may have minimum non-specific effects [64, 65]. We chose to apply a sham device in the sham group to ensure the precision of the results.

Non-invasive neuroimaging technology is the most commonly recommended diagnostic tool in stroke [66]. Technologies such as fMRI open a window for the study of insomnia after stroke. Some researchers have found that patients with primary insomnia have abnormal brain metabolism and connectivity related to particular brain regions, such as the prefrontal cortex, insular cortex, amygdala, precuneus, and caudate [67, 68]. Thus, we can utilize fMRI to assess aspects of treatment-induced changes in resting-state brain metabolism and elucidate the possible underlying mechanisms of these therapies in this protocol.

Melatonin is a hormone secreted by the pineal body, with peak secretion at night [69]. Some researchers have found that abnormal secretion of melatonin is potentially related to insomnia in stroke patients [70, 71]. A preliminary report revealed that acupuncture increased nocturnal melatonin secretion and reduced insomnia and anxiety [72]. We will detect the nocturnal melatonin concentrations in patients with post-stroke insomnia to investigate whether EA plus SZRD can also play a beneficial role by increasing nocturnal melatonin secretion and reducing insomnia.

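### One 3:00 a.m. melatonin concentration per assessment cannot show a change in nocturnal secretion; the mechanism conclusion should be limited to the 3:00 a.m. concentration

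*Protocol article*

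**What the plan says.** The outcome section on nocturnal melatonin sets one sampling time: "Blood samples of patients will be collected at 3:00 a.m. in a dimly lit environment to diminish the impact of light on the secretion of" the hormone. On frequency it says: "Each participant will be assessed at baseline (before treatment) and during the 4th week of the intervention". Each participant therefore contributes two values, both taken at the same clock time. The section heading, the Abstract and the abbreviation list all call the outcome a concentration.

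The Discussion goes a step further. It also speaks first of detecting concentrations, but gives the purpose as to "investigate whether EA plus SZRD can also play a beneficial role by increasing nocturnal melatonin secretion and reducing insomnia". The Objectives section makes a preliminary look at mechanism one of the trial's aims, and the limitations paragraph of the Discussion names melatonin, with MRI, as a means to that aim.

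Two further statements bear on the point. The Discussion says: "Melatonin is a hormone secreted by the pineal body, with peak secretion at night". The outcome section says: "Melatonin coordinates circadian rhythms and regulates sleep function". By the protocol's own account, then, the level changes over the night and is tied to body-clock timing.

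**The concern.** Secretion over a night is an amount. A concentration at 3:00 a.m. is one point on a curve. Two patients who secrete the same amount will have different 3:00 a.m. values if their curves peak at different times. One patient's value will change between baseline and week 4 if the curve moves, even when the amount does not.

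Sampling in dim light deals with light exposure and does nothing about the position of the curve. The article describes no serial sampling, urinary metabolite or marker of rhythm phase, and no later analysis of these two samples can recover the total.

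What is at stake is the wording of the mechanism conclusion. A higher 3:00 a.m. value under the combination could mean more secretion, a curve moved closer to 3:00 a.m., or both. An unchanged value could hide a real rise.

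**Working it through.** **Figure in the plan.** There is none to reproduce. The article gives no melatonin mean, SD, effect size or power; the sample size rests on PSQI alone.

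**Inputs from the article.** Clock time 3:00 a.m.; two assessments (baseline, week 4); secretion peaks at night.

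**Assumed inputs (illustration only).** A bell-shaped overnight curve with SD *s* = 2, 2.5 or 3 h, and a peak time *p* of 3:00 or 4:00 before treatment. Total secretion and *s* are held fixed; only *p* moves.

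**Formula.** The 3:00 a.m. value as a fraction of the peak is f(p) = exp(-(3 - p)² / (2s²)). If the peak moves from p to p′ with the amount unchanged, the relative change in the 3:00 a.m. value is f(p′)/f(p) - 1.

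**Worked case, s = 2.** Peak 4:00 moving to 3:00: exp(0) / exp(-1/8) - 1 = exp(0.125) - 1 = +13.3%. Peak 4:00 moving to 5:00: exp(-4/8) / exp(-1/8) - 1 = exp(-0.375) - 1 = -31.3%.

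| Move of the peak | s = 2 h | s = 2.5 h | s = 3 h |
|---|---|---|---|
| 4:00 to 3:00 | +13.3% | +8.3% | +5.7% |
| 4:00 to 5:00 | -31.3% | -21.3% | -15.4% |
| 3:00, 1 h either way | -11.8% | -7.7% | -5.4% |
| 3:00, 2 h either way | -39.3% | -27.4% | -19.9% |
| 4:00 to 2:00 | 0% | 0% | 0% |

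A peak at 2:00 gives the mirror image of a peak at 4:00.

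**Masking.** The true rise in secretion that a shift would exactly cancel is f(p)/f(p′) - 1. For a 1-hour delay from a 3:00 peak this is 13.3%, 8.3% and 5.7% for s = 2, 2.5 and 3. From a 4:00 peak it is 45.5%, 27.1% and 18.1%.

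**Reading.** With the amount constant, the 3:00 a.m. value can rise, fall or stay the same. The last row shows a 2-hour shift that leaves no trace at 3:00 a.m. The exact percentages depend on the assumed shape. The qualitative result does not: on any curve that varies overnight, one value cannot separate amount from timing.

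**The case against.** The strongest reply is that the outcome is already defined as a concentration almost everywhere, and that secretion enters only as something to investigate, in a Discussion sentence. No outcome definition or statistical section commits the trial to a secretion conclusion. A fixed clock time in dim light, repeated within each patient, is a coherent standardisation. All of this stands, and it makes the point small. It does not remove it, because that sentence states what the measurement is for, and the measurement cannot deliver it.

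Several stronger readings are tempting and are not supported:

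- *A change in sleep timing would be reported as a change in secretion.* The arithmetic moves the melatonin curve, not sleep. Sleep timing matters only so far as the melatonin rhythm moves with it, and the article does not say that it does. The polysomnography statement that "the sleep time of participants will be based on their habit" concerns the laboratory nights. Nothing places the blood draw on those nights, and keeping a habitual sleep time is no evidence that timing changes by week 4.
- *The arm comparison is biased.* Randomisation balances rhythm timing at baseline in expectation. Bias as a measure of secretion needs a shift caused by treatment. That is possible for therapies aimed at sleep, but the article does not show that either treatment produces one.
- *Differences in timing between patients add large noise.* Peak times that differ between patients do spread the values at a single assessment. Timing that is stable within a patient is largely taken out once the baseline 3:00 a.m. value is used, so that spread is not the noise in a baseline-adjusted comparison.
- *The plan wrongly omits a sleep-timing covariate.* Covariates for a secondary biomarker are commonly left to the analysis plan, which is not shown, so this is no finding.

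**Conclusion.** The point holds in a narrow form. The protocol samples melatonin at one clock time per assessment, and its Discussion means to draw from this an inference about nocturnal secretion that such a sample cannot support. A treatment-related shift in the melatonin rhythm could mimic or mask a change in secretion.

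The size is unknown. In the illustration, a 1-hour shift changes the 3:00 a.m. value by -31% to +13% with secretion constant. These figures rest entirely on the assumed shape, width, peak time and shift.

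A reader might infer that the melatonin result will be wrong or uninterpretable. The documents do not support that: a randomised comparison of 3:00 a.m. concentrations remains valid as a comparison of 3:00 a.m. concentrations. The point is minor and concerns one secondary, mechanistic outcome. The PSQI and polysomnography conclusions are untouched.

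**What to change.** 1. Define the outcome as *melatonin concentration at 3:00 a.m.* in the outcome section, and use the same term in the Discussion.
2. Limit the mechanism conclusion to that concentration, and remove the inference about secretion from the Discussion.
3. Compare arms on the week-4 value adjusted for the baseline 3:00 a.m. value, which is already collected.
4. Optionally, report the change in polysomnographic sleep timing by arm as description. State that it measures sleep timing and not melatonin phase. Adjusting for baseline sleep midpoint would not resolve the problem, since a baseline covariate cannot remove a shift that occurs after treatment starts.

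The cost is a few words in the protocol and one model term from existing data, with no extra samples or visits. The only downside is a slightly narrower claim about mechanism.
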